### Description and tracking process of study outcomes

The primary targeted outcome of this study is achieving ≥80% coverage of appropriate pneumonia management and will be assessed using a structured quantitative household survey tool. Three cross-sectional surveys (baseline, midline and endline) will be conducted with caregivers of under-five children who experienced pneumonia-like symptoms in the previous 28 days. These surveys will capture whether care was sought from appropriate sources and whether treatment received aligned with the national guidelines. The success of this research will be when at least 80% of these children:

Received care from appropriate sourcesWere managed according to the recommended national protocols with ≥80% compliance to the prescribed treatment.

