### Sample size

A recent study in the same district found that the prevalence of pneumonia among under-five children in the last 2 weeks was around 5%.^15^ Currently, approximately 25% of under-five children seek appropriate care for ARI, indicating a programme coverage of around 25%.^5 16^ With the introduction of the new implementation strategy, we expect an increase in pneumonia treatment coverage by 80%. To account for potential non-response and to estimate 80% coverage of appropriate treatment at baseline and end-line surveys for under-five children with pneumonia cases (as per the operational definition), a conservative sample size of 120 is to be included. Additionally, based on these assumptions, the estimated sample size at a 5% level of significance for each survey (baseline and end-line), and a varied range of coverage is shown in figure 2.

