**Figure 2 F2:**
[figure not shown]
Sample size estimation.

The total number of children to be surveyed is calculated based on a prevalence rate of 5%, resulting in an estimated sample size of 2400.^5^ Considering the proportion of 5-year-olds in the population (12% based on census data) and the average household size (4.8 as per the NFHS 5 report for Haryana), the number of households to be covered is calculated as 4167 households.^17^ These households will be selected using Probability Proportional to Size (PPS) sampling methods from the defined study area served by the 10 HWCs.^18^ Since community-level healthcare workers maintain a list of under-five children in each household, systematic random sampling will be used to select children within the chosen households.

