The research findings from the learning block will be used to enhance Model 0+, leading to the development of Model 1. Subsequently, a series of rapid cycles involving concurrent implementation, monitoring and strategy refinement will be conducted in the remaining six HWCs. These iterations will take place in multiple co-design workshops, with significant involvement from government authorities. The iterative process will continue until an optimised and comprehensive strategy/model is achieved with the potential for achieving high coverage and quality of pneumonia management among under-five children in the study areas (figure 4). The model will be considered optimised when the healthcare providers can consistently recognise pneumonia signs and symptoms and manage cases in accordance with the national guidelines, with ≥80% fidelity among the suspected cases visiting the centres. Second, treatment compliance among under-five children reaches at least 80%, who have received this treatment from the health facilities.

Once the model is optimised, it will be scaled up to all ten HWCs in the study area. During this scale-up phase (estimated to last 7–8 months), we will continue to monitor both implementation barriers and quantitative indicators such as fidelity to the guidelines and treatment compliance. At the conclusion of the scale-up phase, an endline household survey will be conducted using PPS sampling to identify 120 under-five children who had pneumonia symptoms in the past 28 days. These data will be compared with baseline measurements to assess changes in key outcome indicators, i.e. under-five pneumonia cases receiving management (as per the national guidelines) from the appropriate health facilities, which determines the coverage of appropriate pneumonia management.

The final findings will be shared with state- and district-level health authorities in Haryana. If the district government expresses interest and supports the approach, the model, having already been scaled up within the study area, may be adopted for implementation across the entire Palwal district, with continued technical support from the research team.

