### Data management and data analysis

#### Quantitative data

The study’s data management will be handled by a data management centre (DMC) located in the study field office. The DMC will be using the Research Electronic Data Capture, which is a secure web application for building and managing clinical research data. It is a powerful and flexible tool for data management that can help streamline the research process and improve data quality. The quantitative data will be managed and reviewed by the respective team coordinators, and the data entry system will have inbuilt range and consistency checks. Cross-sectional survey data will be collected electronically and transferred in real-time to a local server at the DMC, where checks across forms and logical error checks will be run. Queries will be generated for the study team’s resolution, corrections will be incorporated into the cleaned data set and the tables for quality assurance will be generated at the Society for Applied Studies (SAS) office in Delhi daily.

Four types of data will be collected: (i) health systems data, (ii) routine patient data, (iii) cross-sectional household survey data and (iv) information on knowledge of pneumonia signs and symptoms and its management. Descriptive and inferential statistical analyses will be performed, including simple proportions and generalised linear models, using the univariate and multivariate regression analyses. The study will determine the prevalence of pneumonia, overall coverage of pneumonia treatment, compliance to treatment and treatment failure and identify predictors of treatment failure.

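### Success is judged by comparing observed endline coverage with 80%, with no allowance for sampling error, although 120 cases are planned around an expected coverage of exactly 80%

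*Protocol article*

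**What the plan says.** **Target and success rule.** Under *Description and tracking process of study outcomes*, the protocol article states: "The primary targeted outcome of this study is achieving ≥80% coverage of appropriate pneumonia management". The same section defines success: "The success of this research will be when at least 80% of these children" received care from appropriate sources and were managed to national protocol with at least 80% compliance. The primary objective repeats the 80% figure. No interval, test or null value is attached in any of these places.

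**Size.** *Sample size* puts current coverage at about 25% and sizes each survey to estimate 80% coverage: "a conservative sample size of 120 is to be included". Non-response is the only allowance named in the text. Figure 2, which holds the sample sizes over a range of coverage, is not shown. *Implementation strategy* repeats the number for the endline survey, "using PPS sampling to identify 120 under-five children who had pneumonia symptoms in the past 28 days".

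**Design and analysis.** *Sample size* says that households will be "selected using Probability Proportional to Size (PPS) sampling methods from the defined study area served by the 10 HWCs". The sampling unit and the number of clusters are not given. *Quantitative data* lists the methods as "including simple proportions and generalised linear models, using the univariate and multivariate regression analyses".

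**The concern.** The pass mark and the expected coverage are the same number. An observed proportion from 120 cases carries several percentage points of sampling error, and the rule reads it as if it had none. When true coverage is near 80%, chance then largely decides which side of the line the estimate falls on, and the reader is told success or failure with no sign of that.

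The verdict matters beyond this report. The article says that the model may be adopted across Palwal district and can be applied in similar settings. A programme that falls a few points short could be put forward as having met its target, and one that met it could be reported as having failed.

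The sampling design raises a second, conditional point. If cases cluster within the sampling units, the uncertainty that should go with the verdict is larger than a simple-random-sample interval shows.

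**Working it through.** **Inputs from the article:** threshold 80%; expected coverage 80%; baseline coverage about 25%; 120 cases per survey; 5% significance level; prevalence 5%; 12% of the population under five; household size 4.8; 10 HWCs; 42 villages. **Assumed, because the article gives no value:** ICC 0.05 to 0.10; either the 42 villages or the 10 HWC areas as clusters.

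**1. The plan's own figures.** 120 / 0.05 = 2400 children. 2400 / (0.12 × 4.8) = 4166.7, rounded up to 4167 households. Both reproduce. The 120 itself cannot be tested, since neither the precision sought nor the non-response rate is in the text. It is consistent with a precision calculation: 1.96² × 0.80 × 0.20 / d² gives 120 at d = 0.0716 with no inflation, or 97 at d = 0.08, which becomes 121 after 20% non-response. A comparison of 25% with 80% needs only about 12 to 22 per survey, so 120 was not driven by the before-after test.

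**2. How the success rule behaves.** Success means at least 0.80 × 120 = 96 children. P(X ≥ 96) for X ~ Binomial(120, p):

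| True coverage | P(success declared) |
|---|---|
| 70% | 0.009 |
| 75% | 0.12 |
| 77.5% | 0.30 |
| 80% | 0.55 |
| 82.5% | 0.80 |
| 85% | 0.95 |

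If the two listed conditions are separate 80% marks that must both be met, the probability at exactly 80% on each lies between 0.55² = 0.31 (independent) and 0.55 (fully overlapping).

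**3. What the data can show.** The normal half-width is 1.96 × √(0.80 × 0.20 / 120) = 0.072. Wilson 95% intervals, [p + z²/2n ± z√(p(1−p)/n + z²/4n²)] / (1 + z²/n):
- 96/120 (80.0%): 72.0% to 86.2%.
- 104/120 (86.7%): lower limit 79.4%.
- 105/120 (87.5%): lower limit 80.4%, the first count that clears the target.
- 87/120 (72.5%): upper limit 79.7%.
- 88/120 (73.3%): upper limit 80.4%.

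Under simple random sampling, counts from 88 to 104 therefore leave the target undecided.

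**4. Clustering, conditional.** Design effect = 1 + (m − 1) × ICC; half-width = 1.96 × √(0.16 × design effect / 120).
- 42 villages, m = 120/42 = 2.9: design effect 1.09 to 1.19, half-width 7.5 to 7.8 points.
- 10 HWC areas, m = 12: design effect 1.55 to 2.10, half-width 8.9 to 10.4 points.

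In a beta-binomial simulation with ten clusters of 12, P(success) at a true 80% stays at 0.55. At a true 75% it rises from 0.12 to between 0.18 and 0.22 over the same ICC range.

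**5. Before-after comparison.** With 120 per survey at 25% against 80%, power stays above 99.9% even at a design effect of 3.

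**The case against.** **The 80% is a programme benchmark, not a hypothesis test, and any threshold gives about even odds when the truth sits on it.** Both are true. Away from the line the rule discriminates well, with 0.95 at 85% and 0.009 at 70%. What remains is the band of a few points around the target. The plan itself expects coverage there, and the article makes the bare comparison its definition of success.

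**Requiring a lower limit of at least 80% would change the target.** This stands. With 120 cases that rule alone would declare success with probability 0.02 at a true 80%, 0.27 at 85% and 0.86 at 90%. It should not become the only favourable conclusion.

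**Clustering and variance may be handled elsewhere.** This also stands. A reader might infer that the stated analysis treats children as independent and so yields intervals that are too narrow. The article does not say so. It names generalised linear models beside simple proportions, and these can carry cluster-robust or random-effect terms. Variance estimation may sit in a full protocol or analysis plan not shown, and a design effect may be in Figure 2. Care also counts from private clinics and higher facilities, which may weaken correlation within an HWC area.

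**The catchment is finite.** The survey takes about 2400 of 9897 under-fives (24%). If the target is coverage in this catchment alone, an approximate correction multiplies the variance by 0.76, and the 42-village half-width becomes 6.5 to 6.8 points. That is a fair reading, but the article also intends the result to inform wider adoption, where the correction would not apply. Either way, an observed 80% stays well inside the undecided range.

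**Conclusion.** The point holds for the success rule. The article fixes a verdict that ignores sampling error, at a pass mark equal to the expected coverage. With 120 cases under simple random sampling, a true 77.5% is called a success three times in ten and a true 80% is called a failure 45% of the time. An observed 80% is compatible with anything from 72% to 86%. None of this needs an ICC.

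The clustering part is conditional. If the interval ignores the PPS design and the ICC is positive, it will be too narrow. The effect is small if all 42 villages are the units and material if the ten facility areas are, at an assumed ICC of 0.05 to 0.10. The documents do not show which applies, so they do not support a flat statement that the planned error bars are wrong.

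Nor should a reader infer that the before-after comparison is at risk: at the planned 25% against 80% its power is ample under every design effect considered.

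**What to change.** 1. Keep 80% as the programme benchmark. Report endline coverage with a 95% CI and word the conclusion from it: **target demonstrated** if the lower limit is at least 80% (from 105/120 under simple random sampling); **not reached** if the upper limit is below 80%; otherwise **compatible with the target but not demonstrated**.
2. Compute the interval from the PPS design, with weights where selection is unequal and the primary sampling unit as cluster. Name that unit.
3. State the precision of 120 cases in place of the word conservative: about ±7 points under simple random sampling. Add the clustered range that applies: about ±7.5 to ±7.8 with 42 villages, or ±8.9 to ±10.4 with ten facility areas, at an assumed ICC of 0.05 to 0.10.

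This needs no new data and no larger sample. It takes a few sentences in the analysis plan or report and routine survey-analysis code, so it remains usable after endline fieldwork. The price is that an outright claim of success becomes harder to make, and an estimate at or just above 80% would be reported as undecided.

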### Data collection for monitoring progress

To monitor progress towards the coverage target, both quantitative and qualitative data will be collected at community and facility levels:

**Community-level quantitative data** (via household cross-sectional survey) will specifically include:**Facility-level data** will be collected at baseline (Phase-I), then bi-monthly (Phase-II and III) and finally at end-line through a cross-sectional survey. This will include:

The source of treatment for pneumonia, time to treatment-seeking after symptom onset, type of treatment received (with verification of medicines/injections where possible), compliance with treatment, reported treatment outcomes out-of-pocket expenses incurred.

**Community-level qualitative data** will include caregivers’ knowledge of pneumonia signs and symptoms, care-seeking behaviour and reasons for provider preference, barriers and enablers to accessing appropriate care, experiences with service delivery and any suggestions to improve pneumonia care services.

**Facility-level data** will be collected at baseline (Phase-I), then bi-monthly (Phase-II and III) and finally at endline through a cross-sectional survey. This will include the number of suspected pneumonia cases presenting at health facilities; number of cases diagnosed, treated or referral made as per guidelines; number of household (diagnosed cases of pneumonia) follow-ups conducted by ASHAs; availability of essential medicines and supplies; status of key equipment (eg, pulse oximeters, thermometers, weighing scales, stethoscopes); human resource availability; and training status of healthcare workers in pneumonia management.

These data streams will allow ongoing tracking of both outcome-level changes (ie, coverage and compliance) and process-level improvements (ie, facility readiness, staff capacity), helping inform adaptive changes to ensure progress towards the final targeted outcome.

### Intervention package

The intervention package will be aligned with the GoI guidelines, which include early identification of pneumonia cases through ASHAs and empowering families, prompt care-seeking from appropriate providers for pneumonia treatment and prompt referral of severe pneumonia cases with pre-referral treatment. At the outpatient department (OPD) of facilities (HWCs/PHCs/CHCs/DH), treatment providers need to be available, be competent and have access to appropriate logistics (equipment, regular supplies of medicines). Pulse oximeters will be provided at the OPDs of these facilities to assess oxygen saturation for improved assessment/evaluation of severe cases requiring referral.

For children, (0–59 days) with PSBI, a prereferral dose of gentamicin and amoxicillin will be provided by the health workers at the HWCs, and then cases are referred to higher facilities. But if a referral is not possible/denied, the package also aims to provide treatment to children aged 0 to 59 days in the outpatient department of primary-level care. In cases where caregivers are unable to bring their infants to the health facilities for the full course of injection, gentamycin and oral amoxicillin for 7 days will be provided by the auxiliary nurse midwives to cases (0–59 days) at home.^4 19 20^

In discussions with the government, strategies will be finalised to promote treatment in female children, such as providing additional incentives to ASHAs for referring or accompanying girl children for pneumonia treatment, free transportation for girl children to facilitate referral for outpatient treatment and providing free food or compensating daily wages lost due to hospital admissions.

At the post-facility level, ASHAs will be rewarded (with government consensus) for ensuring full compliance with the treatment course in female children. The decision to address the appropriate treatment of pneumonia in the private sector, where many children with pneumonia seek care, by involving private providers in the discussion with the government partners, will be based on the formative research findings. Appropriate use of bronchodilators in children with wheeze at health facilities and identification of conditions mimicking pneumonia for rational therapy will also be included. Finally, recognition of cases that do not have pneumonia and do not require antibiotics but may benefit from supportive treatment.

In the process, all collateral programmes supporting pneumonia management will be strengthened like Janani Shishu Suraksha Karayakram (for free transportation, medicines and diagnostics test availability), Comprehensive Primary Healthcare (strengthening care at HWCs) and HBNC (improving the quality of care by ASHAs). All the activities will be conducted with deep government engagement. The conceptual framework of implementing this intervention is summarised in figure 3.

**Figure 3 F3:**
[figure not shown]
Conceptual framework for increasing coverage of pneumonia treatment. ANM, auxiliary nurse midwife; ASHA, accredited social health activist; CHC, Community Health Centre; HWC, Health and Wellness Centre; OPD, outpatient department; PHC, primary healthcare; RR, respiratory rate.

### Research teams

There will be three teams: (i) the Implementation Support Team (IST), (ii) the Programme Learning Team (PLT) and (iii) the Outcome Measurement Team (OMT).

The IST will provide technical support to government partners and assist in programme implementation. They will facilitate government staff training in the study area, identify process gaps for refinement and develop tools and job aids. Additionally, the IST will support community awareness activities and data collection from ASHA records and healthcare facilities.

The PLT, composed of qualitative researchers, will assess fidelity and compliance through methods like focus group discussions (FDGs), in-depth interviews (IDIs) and observations. They will provide prompt feedback to the IST and deliver weekly reports.

The OMT will focus on measuring primary and secondary outcomes. They will conduct baseline and endline cross-sectional surveys in randomly selected households within the study area, assessing population-based programme coverage using a randomised sample selection method.

### Implementation strategy

The implementation plan for promoting the treatment of pneumonia in under-five children will follow a systematic approach involving formative research, engagement of key stakeholders, model development, implementation and evaluation (figure 4). The study will consider the GoI childhood pneumonia guidelines and develop model 0 through expert consensus. IDIs and FDGs will be conducted to gain a comprehensive understanding of stakeholders’ perspectives, knowledge and practices related to pneumonia management. For the implementation of guidelines, the key stakeholders, including mothers/primary caregivers, healthcare workers, community health workers and government partners, will be identified and actively engaged in the study catchment area.

**Figure 4 F4:**
[figure not shown]
Iterative cycles of model optimisation.

The formative research (phase-I) findings will be analysed to identify pneumonia management barriers and facilitators, and a Model 0+implementation strategy will be developed. This model will include strategies to create caregiver awareness, encourage care-seeking at appropriate health facilities, improve community health workers’ skills in case identification and referrals and provide training and capacity building for other healthcare workers to enhance early identification and treatment of pneumonia cases. Workshops will be conducted with the research team and government partners to refine and finalise Model 0+ for local alignment and needs.

Following the development of Model 0+ will be implemented in a learning block comprising four randomly selected HWCs, with the close collaboration of government partners, to provide initial handholding and support for implementation. Monitoring and evaluation of process indicators such as access, utilisation, compliance, adherence and fidelity to childhood pneumonia management guidelines, as well as health facility components like infrastructure, human resources, delivery, availability of medicines and supplies, and documentation, will be conducted. Evaluation data will be analysed and shared with the government implementation team monthly to guide decision-making. Any inconsistencies identified between the evaluation data and existing system data will be addressed through corrective actions.

The research findings from the learning block will be used to enhance Model 0+, leading to the development of Model 1. Subsequently, a series of rapid cycles involving concurrent implementation, monitoring and strategy refinement will be conducted in the remaining six HWCs. These iterations will take place in multiple co-design workshops, with significant involvement from government authorities. The iterative process will continue until an optimised and comprehensive strategy/model is achieved with the potential for achieving high coverage and quality of pneumonia management among under-five children in the study areas (figure 4). The model will be considered optimised when the healthcare providers can consistently recognise pneumonia signs and symptoms and manage cases in accordance with the national guidelines, with ≥80% fidelity among the suspected cases visiting the centres. Second, treatment compliance among under-five children reaches at least 80%, who have received this treatment from the health facilities.

Once the model is optimised, it will be scaled up to all ten HWCs in the study area. During this scale-up phase (estimated to last 7–8 months), we will continue to monitor both implementation barriers and quantitative indicators such as fidelity to the guidelines and treatment compliance. At the conclusion of the scale-up phase, an endline household survey will be conducted using PPS sampling to identify 120 under-five children who had pneumonia symptoms in the past 28 days. These data will be compared with baseline measurements to assess changes in key outcome indicators, i.e. under-five pneumonia cases receiving management (as per the national guidelines) from the appropriate health facilities, which determines the coverage of appropriate pneumonia management.

The final findings will be shared with state- and district-level health authorities in Haryana. If the district government expresses interest and supports the approach, the model, having already been scaled up within the study area, may be adopted for implementation across the entire Palwal district, with continued technical support from the research team.

